|                                      | 
 
- QTc <math>\leq</math> 450 ms
 
- ECOG performance status of <math>< 3</math>
 
- Capable of understanding the study and giving informed consent
 
- Negative COVID-19 test at study entry as measured by routine testing (not older than 28 days)
 
                                                                                                                                                                                                                     |
| EXCLUSION CRITERIA (SYNOPSIS) | 
 
- Use of any investigational agent within 28 days prior to study start
 
- Patients with active opportunistic infections
 
- Pregnant or lactating women
 
- Women of childbearing potential and male subjects not willing to use adequate contraception methods during the study period
 
- Hypersensitivity to azithromycin or other macrolides
 
- Concurrent medication with ergotamine, theophylline, digitalis
 
- Inability to swallow tablets
 
 |
| TEST DRUG (IMP) / TREATMENT   | 
Azithromycin, applied as long-term treatment at once weekly dose of azithromycin 1500 mg (i.e. 3 x 500 mg on one day) orally.
 
Patients will be randomized to azithromycin monotherapy given orally once weekly at a dose of 1500 mg versus placebo. Treatment will last for a maximum of 8 weeks in the absence of documentation of SARS-COV-2-infection.
                                                                                                                                                                           |
| PRIMARY ENDPOINT              | 
 
- Cumulative number of SARS-COV-2 infections (symptomatic or asymptomatic) as assessed by positive PCR from routine nasal swabs (performed every 28 days) at 12 weeks after initiation of therapy
 
                                                                                                                                                                                                                                                                                               |

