#### Primary endpoints:

- Cumulative number of SARS-COV-2 infections as verified by PCR from routine nasal swabs performed every 28 days (symptomatic or asymptomatic) at week 12 after initiation of therapy

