## 6. OUTCOME PARAMETERS

### 6.1 Definition of the primary endpoint

Number of SARS-COV-2 infections (symptomatic or asymptomatic): detected by routine SARS-COV-2 tests in all patients treated at the Division of Oncology, Medical University of Vienna. During the SARS-COV-2 pandemic, the routine approach to patients undergoing chemotherapy at our institution is PCR from nasal swabs taken every 28 days. The cumulative number of infections detected (symptomatic or asymptomatic) at week 8 after initiation of therapy in both treatment arms serves as the primary endpoint.

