| 20                                         | 52%                        | 81% | 93% | 98% | 99% |

**Recruitment period:** Recruitment period 4 Weeks (50 patients per week), follow-up 12 weeks  
After 200 follow-up tests have been performed (around week 8), an interim and safety analysis will be performed. If very low infection rates, i.e. less than one infection, are observed the trial may be stopped for futility. If the results are promising, the trial might be extended (further details see in section on statistical analysis).

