## Primary Endpoint Analysis

All primary analyses will be on the ITT set and the analysis based on the per protocol set will be provided as supportive analysis. The primary endpoint is the between group difference in the incidence rate per 4 weeks. We will compute 2-sided 95% confidence bounds for the incidence rates. Furthermore, we test the null hypothesis that the incidence rates in the two groups are equal. To estimate and compare the incidence rates, the test status at weeks 4,8,12 will be modeled using time to event analysis models and will adjusted for calendar time to account for time trends in the incidence rate. The time-to-infection is defined as time from randomization to infection. If patients drop out, their observations will be censored at the last observation time.

This data will be visualized by Kaplan-Meier Plots. For each group unadjusted two-sided 95% confidence intervals will be reported as well.

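### Section 6.1 sets the primary endpoint at week 8, whereas the synopsis, Section 3.1 and the primary analysis in Section 10.2 run to week 12

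*Protocol*

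**What the plan says.** Four places in the protocol describe the primary endpoint.

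- **Synopsis, primary endpoint:** a cumulative number of infections, "as assessed by positive PCR from routine nasal swabs (performed every 28 days) at 12 weeks after initiation of therapy".
- **Section 3.1, primary endpoints:** the same count, "symptomatic or asymptomatic) at week 12 after initiation of therapy".
- **Section 6.1, definition of the primary endpoint:** the same count, but "at week 8 after initiation of therapy in both treatment arms serves as the primary endpoint".
- **Section 10.2, primary endpoint analysis:** "The primary endpoint is the between group difference in the incidence rate per 4 weeks". For this, "the test status at weeks 4,8,12 will be modeled using time to event analysis models", with adjustment for calendar time. The clock also differs: "The time-to-infection is defined as time from randomization to infection". The other three places count from the start of therapy.

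Three other statements bear on the horizon. The synopsis puts its hypothesis of at least a 30% reduction at week 12. Section 10.1 plans "Recruitment period 4 Weeks (50 patients per week), follow-up 12 weeks". Section 3.1 limits study treatment to 8 weeks.

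**The concern.** The section titled as the definition of the primary endpoint is the one that disagrees with the rest, and the protocol has no rule for which text takes precedence. A reader who goes to Section 6.1 for the definition would count infections to week 8. A reader who goes to the synopsis, Section 3.1 or Section 10.2 would count them to week 12.

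The two horizons do not measure the same thing. Week 8 is essentially the on-treatment period. Week 12 adds about a month without study drug. If protection fades when treatment stops, week 12 shows a diluted effect. If protection lasts, week 12 has more events and is the more informative. The two can give different results, and the primary result should not depend on which section is read.

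A smaller mismatch lies beside this. A cumulative number counted from the start of therapy and a difference in incidence rate counted from randomization are different summaries of the same infections, and the protocol calls each of them the primary endpoint.

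**Working it through.** **1. The places side by side**

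| Place | Quantity | Horizon | Time origin |
|---|---|---|---|
| Synopsis | cumulative number | week 12 | start of therapy |
| Section 3.1 | cumulative number | week 12 | start of therapy |
| Section 6.1 | cumulative number | **week 8** | start of therapy |
| Section 10.2 | difference in rate per 4 weeks | tests at weeks 4, 8, 12 | randomization |

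There are two horizons. The 4 weeks in Section 10.2 are the unit of a rate, which matches the 28-day swab interval, and its data run to week 12.

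**2. Do the horizons cover different treatment periods?** Section 7.2 gives doses on days 1, 8, 15 and 22 of two 28-day cycles. The last planned dose is on day 28 + 22 = 50, and the second cycle ends on day 56. Week 12 is day 84. The difference is 84 − 56 = 28 days off treatment.

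**3. How far apart are the time origins?** Section 3.2 allows randomization at most 3 days before treatment start. The gap is therefore at most 3 of 84 days, or 3.6%. It is small, but it should be stated one way.

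**4. The plan's own figures** (Section 10.1: 100 per arm, two-sided 0.05, pooled chi-squared test)

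- 40% versus 60%: power 81.2% (stated: at least 81%).
- 42.5% versus 57.5%: power 56.5% (stated: at least 56%).
- Confidence interval half-width: 1.96 × √(2 × 0.25/100) = 0.139 (stated: 0.14).

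These reproduce. Section 10.1 attaches no time point to the proportions.

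**5. Illustration: the same effect read at each horizon.** Assumptions not in the protocol: a constant hazard in each arm, and the 50% versus 30% example taken as week-12 risks.

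- Hazard per 4 weeks = −ln(1 − risk)/3, giving 0.231 (control) and 0.119 (azithromycin). The rate difference is 0.112 per patient per 4 weeks.
- Week-8 risk = 1 − exp(−2 × hazard), giving 37.0% and 21.2%. The difference is 15.8 points and the power 69.7%.
- Week 12: 50% versus 30%. The difference is 20.0 points and the power 82.8%.
- At a lower assumed risk, 10% versus 7% at week 12, the differences are 3.0 points (week 12), 2.1 points (week 8) and 0.011 per 4 weeks.

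**6. Illustration: the effect ends with treatment.** Assumptions: a constant baseline hazard, a 30% hazard reduction for 8 weeks and none afterwards.

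- Average hazard ratio to week 12 = (8 × 0.7 + 4 × 1)/12 = 0.80, so a 30% reduction becomes 20%.
- Ratio of z-statistics, week 8 to week 12 = |ln 0.7| × √8 / (|ln 0.8| × √12) = 1.009/0.773 = 1.31.
- If the effect persists unchanged off drug, week 12 is the stronger, by √(12/8) = 1.22.

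**7. Hypothetical worst case for type I error.** Assumptions: both tests are run, the better one is reported, and events accrue evenly, so that the correlation is √(8/12) = 0.82. For a bivariate normal pair, the probability that either |Z| exceeds 1.96 is 0.077, against 0.05 for a single test.

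**The case against.** The best reply is that Section 6.1 contains one stray number. The synopsis endpoint and hypothesis, Section 3.1, the 12-week follow-up in Section 10.1 and the Section 10.2 model all point to week 12. So does the severe-COVID secondary endpoint in Section 6.2. Only one primary hypothesis test is described, and it uses all three test times. This is a good argument for which way to correct the text. It does not remove the need to correct it, because the stray number stands in the defining section. Week 8 is also not absurd on its face: it coincides with the end of treatment and with the second resistance-swab visit in Section 8.3.

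Four stronger readings may tempt a reader, and the protocol does not support them.

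- **Three competing primary endpoints.** There are two horizons. Section 10.2 is a different summary of the same infections over the 12-week data, not a third time point.
- **The proportions in Section 10.1 as a further endpoint.** That section presents its z- and chi-squared tests as sizing tools and says that the actual analysis will account for time trends.
- **An undefined first-stage p-value for the adaptive extension.** The extension text in Section 10.2 bases it on the time-to-event analysis defined above it, which is the week 4, 8 and 12 model. The data and the class of analysis are fixed there, and further detail is left to the SAP.
- **A type I error that is 7.7%.** That figure needs a free choice after the data are seen, which no section plans, and even event accrual. Section 10.1 itself stresses how unpredictable incidence is.

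**Conclusion.** The contradiction is in the current text and does not depend on any calculation: week 8 in Section 6.1, week 12 in the synopsis and Section 3.1, and tests to week 12 in Section 10.2, with no order of precedence. It concerns the primary endpoint and decides whether four off-treatment weeks count, so it must be corrected. The mismatch in summary measure and time origin between Section 10.2 and the other three places is secondary and can be settled in the same edit.

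The sizes are illustrations only. The 20.0 versus 15.8 points, and 82.8% versus 69.7% power, assume a constant hazard and week-12 risks of 50% and 30%. The dilution from 30% to 20% and the ratio of 1.31 assume a constant baseline hazard and an effect that ends with treatment. The 7.7% is a worst case under a free choice between two tests. The stated power and precision in Section 10.1 reproduce and are not made wrong by this point.

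**What to change.** - Change Section 6.1 from week 8 to week 12.
- Make the synopsis and Sections 3.1, 6.1 and 10.2 state the same primary endpoint, with one horizon (week 12), one time origin and one summary measure consistent with the time-to-event model in Section 10.2. The incidence-rate difference already named there can serve, so no new effect measure is required.
- For the origin, randomization is already used in Section 10.2. It also suits an intention-to-treat analysis of all enrolled patients, because a patient who never takes study drug has no start-of-therapy date.
- Say that the week-12 result includes four weeks after study treatment ends. A week-8, on-treatment estimate may be reported if it is labelled as supportive.

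The cost is amendment wording in those sections. No extra data are needed beyond the week-12 test that Section 10.2 already uses, and the sample size does not change.

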### 6.2 Definition of secondary endpoints

Number of patients experiencing severe COVID-19 infection defined as a combined endpoint of hospitalization or death at week 12 after initiation of therapy.

COVID-19 cases are defined as outlined by the WHO, including a PCR for COVID-19 from any specimen (respiratory, blood, urine, stool, other bodily fluids).

Severity of COVID-19 cases: The severity of cases will be classified as suggested in the Blue Print for COVID-19 therapeutic trials by the WHO (range 0-8)

**Table.** Ordinal Scale for Clinical Improvement of COVID-19 (WHO Blueprint).

| Patient state                 | Descriptor                                                  | Score |
|-------------------------------|-------------------------------------------------------------|-------|
| Uninfected                    | No clinical or virologically evidence of infection          | 0     |
| Ambulatory                    | No limitations of activity                                  | 1     |
|                               | Limitation of activities                                    | 2     |
| Hospitalized – mild disease   | Hospitalized, no oxygen therapy                             | 3     |
|                               | Oxygen by mask or nasal prongs                              | 4     |
| Hospitalized – severe disease | Non-invasive ventilation or high flow oxygen                | 5     |
|                               | Intubation and mechanical ventilation                       | 6     |
|                               | Ventilation + additional organ support – pressors, RRT, ECM | 7     |
| Dead                          | Death                                                       | 8     |

### All cause mortality

### Tolerance and side effects related to azithromycin

### Rate of infections other than COVID-19, i.e. bacterial and viral infections

### Development of azithromycin-resistant bacterial strains:

- ❖ During our study, the influence of the macrolide on resistance of *S. aureus* strains in the nasal flora vs placebo will be assessed by nasal swabs (taken at baseline and then at Visit 1 + 2, i.e. week 4 and 8 latest). *S. aureus* strains will be cultivated on selective agar-plates, then isolated and frozen in Cryo-tubes for resistance testing at a later time-point.
- ❖ *S. aureus* will be cultivated and isolated on Chrom-ID Elite Plates:
- ❖ <https://www.biomerieux.de/klinische-diagnostik/chromidtm-s-aureus-elite-agar-saide>
- ❖ [Testing for resistance will be done phenotypically using a micro-dilution method.](#)

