**Secondary endpoints:**

- To evaluate the capacity of azithromycin to prevent severe COVID-19 infections, defined as a combined endpoint of hospitalization and death in cancer patients undergoing active treatment with chemotherapy
- Severity of COVID-19 cases (see grading as defined by the WHO)
- All-cause mortality
- Safety and tolerability of IMP (clinical and laboratory, CTCAE criteria)
- Occurrence of viral or bacterial infections other than COVID-19
- Development of azithromycin-resistant bacterial strains as assessed by nasal swabs

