### 8.3 Study procedures

#### At baseline (within 28 days prior to first treatment)

- Written informed consent
- Complete medical history including oncological medical record
- Assessment of the oncological treatment plan
- Documentation of concomitant medication

- Physical examination and ECOG status assessment
- ECG including assessment of QTc
- Hematology (complete blood count, differential)
- Routine serum biochemistry including procalcitonin and IL6
- Pregnancy test in women of childbearing-potential
- Nasal swab for resistance testing at baseline

Investigations during the study (study visits on day one of each antineoplastic treatment cycle or on day 28 latest) and at end of treatment

- Assessment of adverse events and concomitant medication
- Hematology (complete blood count, differential)
- Routine serum biochemistry including procalcitonin and IL6
- Pregnancy test in women of childbearing-potential
- ECG with assessment of QTc
- Nasal swab for testing of azithromycin-resistant bacterial strains at Visit 1 and 2 (latest week 4 and 8)

PCR for SARS-COV-2 from nasal swabs taken every 28 days is part of the routine care of patients; however, results will be used for defining infection with SARS-COV-2.

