### Secondary Endpoints

- Number of severe COVID-19 cases defined as combined endpoint of hospitalization rate or death at 12 weeks after initiation of therapy
- Severity of COVID-19 cases (see grading by WHO)
- All-cause mortality
- Safety and tolerability of IMP (clinical and laboratory, CTCAE criteria)
- Infections other than COVID-19 including bacterial and viral infections
- Occurrence of azithromycin-resistant bacterial strains

For **binary secondary endpoints** (such all-cause mortality or number of severe COVID-19 cases) absolute ( $n =$  ) and frequencies in percent (%) will be calculated per treatment group. 95%-confidence intervals will be calculated for rates, if appropriate. Such data will be visualized with bar charts. If appropriate, logistic regression models will be applied using treatment as independent factor. Furthermore, the model will be adjusted for sex and age.

For **ordinally scaled endpoints** (such as Grading of COVID-19 cases on day 0, 28 (=week 4), 56 (=week 8) and 84 (=week 12) after randomization) absolute ( $n =$  ) and frequencies in percent (%) will be calculated for all categories separately for each treatment group (and timepoints. If appropriate, treatment groups will be compared with each other by Mann-Whitney-U Tests.

For **time-to-event endpoints** (such as overall survival (OS)) Kaplan-Meier plots will be provided. The two-group will be compared with log-rank Tests. Additionally, similar analysis as for the primary endpoint will be performed.

The analyses of all secondary endpoints are considered as exploratory. Unadjusted p-values and 95%-confidence intervals might be presented for secondary endpoints, but these are for descriptive purposes only and not subject to adjustment for multiplicity.

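### The resistance endpoint is defined as development from a baseline swab but analysed as occurrence, and its last swab can fall well before dosing ends

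*Protocol*

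**What the plan says.** The synopsis and Sections 3.1 and 6.2 of the protocol all name the endpoint as development of resistance; Section 3.1 has "Development of azithromycin-resistant bacterial strains as assessed by nasal swabs". Section 6.2 restricts it to *S. aureus* and says that "strains in the nasal flora vs placebo will be assessed by nasal swabs (taken at baseline and then at Visit 1 + 2", with weeks 4 and 8 as the latest times. Only cultured isolates are tested: "strains will be cultivated on selective agar-plates, then isolated and frozen in Cryo-tubes for resistance testing at a later time-point".

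The list of secondary endpoints in Section 10.2 changes the term to "Occurrence of azithromycin-resistant bacterial strains". For binary secondary endpoints that section gives counts and percentages per arm and then: "If appropriate, logistic regression models will be applied using treatment as independent factor". It adds: "Furthermore, the model will be adjusted for sex and age". All of this is declared exploratory: "The analyses of all secondary endpoints are considered as exploratory".

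Section 8.3 lists a resistance swab at baseline. The later assessments come under "Investigations during the study (study visits on day one of each antineoplastic treatment cycle or on day 28 latest) and at end of treatment", but the swab entry in that list names only Visits 1 and 2, again with weeks 4 and 8 as outer limits. The synopsis differs twice: it lists the swab among investigations during the study and at the end-of-study visit without the limit to Visits 1 and 2, and its baseline list contains no resistance swab.

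**The concern.** Development means resistance that was absent at entry and present later. Occurrence means resistance that is present. The baseline swab separates the two, and the analysis text gives it no role. An analyst following Section 10.2 literally would count a patient who entered with a resistant strain as an event.

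The swab schedule raises a second problem. Weeks 4 and 8 are ceilings, while the visits follow the patient's antineoplastic cycles. A patient on short cycles reaches Visit 2 with part of the azithromycin course still ahead, so resistance selected late in dosing goes unseen.

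A third matter is conditional. The isolates are recovered while an antibacterial is being given, so whether there is an isolate to test is itself affected by treatment. If the percentage were taken over isolates, loss of susceptible strains would raise it without any new resistance.

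This is the only resistance endpoint in a trial that gives an antibiotic as prophylaxis, so its percentages should have one clear meaning.

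**Working it through.** The protocol states no figure for this endpoint, so there is none to reproduce; the power table in Section 10.1 concerns infection.

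**1. Timing of the last swab.** Section 7.2 gives doses on days 1, 8, 15 and 22 of two 28-day cycles, that is days 1, 8, 15, 22, 29, 36, 43 and 50. The antineoplastic cycle length is an assumption, since the protocol states none; Section 5.2 admits a wide range of regimens. I take the first cycle to start with dosing (Section 3.2), Visit 2 to be day 1 + 2 × cycle length, and the swab to precede any dose due that day.

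| Assumed cycle | Visit 2 | Doses already taken |
|---|---|---|
| 14 days | 1 + 28 = day 29 | 4 of 8 |
| 21 days | 1 + 42 = day 43 | 6 of 8 |
| 28 days | 1 + 56 = day 57 | 8 of 8 |

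Section 5.2 also admits patients already on treatment. Their cycles need not start with dosing, so Visit 2 can come earlier still.

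**2. Mixing prevalent with acquired resistance.** Let *p* be the proportion resistant at entry and still resistant on study, equal in both arms in expectation, and let *a* be the proportion newly resistant. Occurrence compares *p* + *a*(azithromycin) with *p* + *a*(placebo). The expected difference is unchanged, but the ratio is pulled towards 1 and the prevalent cases add noise. With 100 per arm, the standard deviation of the between-arm difference in prevalent cases is √(2 × 100 × *p*(1 − *p*)):

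- *p* = 2%: √3.92 = 2.0 patients
- *p* = 6%: √11.28 = 3.4 patients
- *p* = 12%: √21.12 = 4.6 patients

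These values of *p* are assumptions: carriage of 20–40% times baseline resistance of 10–30% gives 2–12%.

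**3. Choice of denominator.** Let *r* be the share of baseline carriers whose strain is resistant and *k* the fraction of susceptible strains cleared on azithromycin. Suppose the drug causes no new resistance. Per recovered isolate the resistant share is *r* on placebo and *r* / (*r* + (1 − *r*)(1 − *k*)) on azithromycin. Carriage cancels. None of these rates is in the protocol; I take *r* as 10–30% and *k* as 30–80%.

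- Smallest gap: *r* = 0.10, *k* = 0.30 gives 0.10/0.73 = 13.7% against 10%, a difference of 3.7 points.
- Largest gap: *r* = 0.30, *k* = 0.80 gives 0.30/0.44 = 68.2% against 30%, a difference of 38.2 points.
- Middle case, 30 carriers per 100 and *r* = 0.20: placebo 6/30 = 20%; azithromycin 6/18 = 33% at *k* = 0.50 and 6/10.8 = 56% at *k* = 0.80.

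In 4,000 simulated trials per scenario, a nominal 5% chi-squared test on isolates rejected in 18% and 59% of runs for the two middle-case settings, and in 11% to 80% over the four scenarios run. With all 100 patients per arm as denominator, the middle case is 6/100 in each arm and the rejection rate was 4–5% in all four scenarios. New resistance is 0 against 0.

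**The case against.** A reader might infer that the endpoint as written will show resistance caused by the drug where there is none. The protocol does not support that.

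- Baseline resistance is balanced in expectation by 1:1 randomisation against placebo, so it raises occurrence in both arms alike.
- Section 6.2 describes laboratory work and fixes no denominator. The rule in Section 10.2, with percentages per arm and adjustment for sex and age, reads more naturally per patient, and per patient the clearance artefact is zero. A higher resistant share through selection could also be a legitimate measure of the macrolide's influence, provided it is labelled as such.
- The endpoint is exploratory, and the denominator and baseline handling may be settled in the statistical analysis plan, which is not shown.
- The change of term could be loose labelling. The other-infections endpoint is also worded differently from section to section.
- The 14- and 21-day cycles are not in the protocol. The heading in Section 8.3 includes end of treatment, and the synopsis places the swab at the end-of-study visit.

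The first two points stand, so the clearance effect can only be stated conditionally. The rest soften the concern without removing it. Development and occurrence are different quantities, and the protocol itself uses both. Swab dates are set in the protocol's procedures, and an analysis plan cannot recover a swab that was not taken. The synopsis wording conflicts with Sections 6.2 and 8.3 and therefore does not settle the timing.

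**Conclusion.** The concern holds in a limited form.

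- **Definition:** the endpoint is defined as development and analysed as occurrence, with no stated use of the baseline swab. The effect is dilution and room for chance imbalance (a standard deviation of about 2 to 5 patients between arms under the assumed rates), not systematic bias towards a drug effect.
- **Timing:** with antineoplastic cycles shorter than 28 days the last swab misses late exposure, after 4 of 8 doses at 14 days or 6 of 8 at 21 days (assumed cycle lengths). Regimen is balanced between arms in expectation, so the harm is missed late resistance.
- **Denominator:** the spurious gap of about 4 to 38 points arises only if isolates are the denominator. Section 6.2 does not exclude that reading, but the protocol nowhere commits to it. The size rests wholly on the assumed resistance and clearance rates.

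The primary endpoint is not affected.

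**What to change.** In Sections 6.2 and 10.2, define the event as a patient with an azithromycin-resistant *S. aureus* isolate at any on-study swab and none at baseline. Take all swabbed randomised patients as denominator and count non-carriers as not resistant. Report *S. aureus* carriage by arm and visit beside it, so that clearance is visible. Use *development* throughout.

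In Sections 6.2 and 8.3, take the second on-study swab at the end-of-treatment visit that Section 8.3 already schedules. Reconcile the synopsis with both sections, on the timing of the later swabs and on the missing baseline swab, which the new definition needs.

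The cost is wording. The number of swabs stays the same and one moves to an existing visit. The drawback is fewer events than a strain-based tally would give, and so less precision.
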